**Fig. 1 Fig1:**
[figure not shown]
Study Schema

Patients will be stratified by two of the strongest prognostic factors, based on a large multi-institutional analysis [3]: histology (Group 1: prostate, breast, or renal; Group 2: all others), and type of pre-specified systemic therapy (Group 1: immunotherapy/targeted; Group 2: cytotoxic; Group 3: observation).

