## Statistical considerations

### Randomization

The study will employ a 1:2 randomization between Arm 1: Arm 2, based on the stratification factors described in Methods/design section. Patients will be randomized in permuted blocks, with the size of the blocks known only to the statistician. The randomization sequence is known only to the statistician and uploaded into a restricted-access database (REDCap) housed on secure hospital servers at LHSC. Upon enrollment of a patient, the database will be accessed by the trial co-ordinator to obtain the next intervention in the random sequence, for the pertinent stratum, which will then be assigned to the patient.

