### Analysis plan

Patients will be analyzed in the groups to which they are assigned (intention-to-treat). De-identified data (except for study number and initials, see confidentiality below) will be transmitted from participating centres via REDCap to be collected centrally where it will be stored on secure hospital servers at LHSC. Source documents will also be uploaded. Research coordinators (clinical trials staff) will perform data checks throughout the trial period and will call participating centres or visit as necessary. PFS and OS will be calculated using the Kaplan-Meier method with differences compared using the stratified log-rank test. Pre-planned subgroup analyses will occur based on the stratification factors. A Cox multivariable regression analysis will be used to determine baseline factors predictive of survival endpoints. For the endpoint of time to new metastases, a Fine and Gray competing risk analysis will be used to account for competing risk of death. Quality of life at 6 months will be measured using FACT-G and EQ-5D-5 L scores, with differences between groups tested using the Student’s t-test. Differences in rates of grade 2 or higher toxicity between groups will be tested using the Fisher’s Exact Test or Chi-Squared test, as appropriate.

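### Grade 2+ toxicity is compared without the randomisation strata: a valid test, but conservative for SABR harm if toxicity differs between strata

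*Protocol article*

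**What the plan says.** Study design sets two stratification factors, histology group and systemic therapy type, the latter with three levels: "Group 1: immunotherapy/targeted; Group 2: cytotoxic; Group 3: observation". The reason given is prognosis: "Patients will be stratified by two of the strongest prognostic factors". The Randomization section states "The study will employ a 1:2 randomization between Arm 1: Arm 2", using permuted blocks, with each allocation taken from the sequence for the patient's own stratum.

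The Analysis plan carries the strata into the survival comparisons: "PFS and OS will be calculated using the Kaplan-Meier method with differences compared using the stratified log-rank test". It does not carry them into the toxicity comparison: "Differences in rates of grade 2 or higher toxicity between groups will be tested using the" Fisher exact or chi-squared test, whichever suits. The quality-of-life t-test is also unstratified.

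Toxicity is a secondary endpoint, graded by NCI-CTC version 4 for each treated organ. The only grade 2+ rate in the article is 29% with SABR in the predecessor trial (Background). There is no control-arm rate, no rate by stratum and no power target for toxicity.

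**The concern.** Blocking within strata holds the arms close to 1:2 in every stratum, so differences in risk between strata contribute almost nothing to the error of the arm difference. A pooled 2x2 test still counts that variation in its standard error. If strata differ in toxicity risk, the standard error is too large and the true size falls below 5%.

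For an efficacy claim that is a harmless form of caution. For a comparison meant to reveal harm, it makes a real excess somewhat easier to report as non-significant. The Background section expects SABR toxicity to rise with the number of lesions, so the comparison matters. The test is named in the article, so this is a stated choice and not a detail left to an analysis plan.

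**Working it through.** **The plan's own figures.** None exists for toxicity. The OS design is not at issue and reproduces. With medians of 10 and 17 months and 1:2 allocation, Schoenfeld's formula at 122 events gives z = √(122 × 2/9) × |ln(10/17)| − 1.96 = 5.207 × 0.5306 − 1.96 = 0.80, or 78.9% power against the stated 80%.

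**Inputs.** From the article: 159 patients at 1:2 (53 v 106) and the three systemic therapy levels. Assumed: two-sided 0.05, stratum shares of 25% observation, 35% immunotherapy/targeted and 40% cytotoxic, the control rates in the table, a constant SABR odds ratio across strata, and no effect of histology on toxicity.

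**Size of the pooled test.** Let w be the stratum shares, p the stratum rates and p̄ = Σwp. With exact balance, the null variance of the arm difference is proportional to W = Σwp(1−p), while the pooled chi-squared uses T = p̄(1−p̄). With R = T/W, the true size is 2Φ(−1.96√R).

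For rates of 10/40/70%:
- p̄ = 0.25×0.10 + 0.35×0.40 + 0.40×0.70 = 0.445
- T = 0.445 × 0.555 = 0.2470
- W = 0.25×0.09 + 0.35×0.24 + 0.40×0.21 = 0.1905
- R = 1.296 and √R = 1.139
- size = 2Φ(−2.232) = 2.6%

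**Power.** The power columns come from simulation at a SABR odds ratio of 2.5 with all six strata, blocks of six and incomplete final blocks (12,000 runs per row). They compare the pooled chi-squared with a six-stratum Cochran-Mantel-Haenszel (CMH) test.

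| Control rates: observation / immunotherapy-targeted / cytotoxic | R | Size of pooled test (formula) | Power, pooled | Power, CMH | Gain (points) |
|---|---|---|---|---|---|
| 30/30/30% | 1.000 | 5.0% | 74.8% | 74.7% | about 0 |
| 30/40/50% | 1.027 | 4.7% | – | – | about 1 (three strata) |
| 20/40/60% | 1.114 | 3.9% | 68.5% | 72.0% | 3.5 |
| 5/20/40% | 1.121 | 3.8% | 58.1% | 64.2% | 6.1 |
| 10/40/70% | 1.296 | 2.6% | 54.0% | 64.7% | 10.7 |
| 5/20/60% | 1.333 | 2.4% | 46.0% | 60.4% | 14.4 |

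In the 10/40/70% row the simulated size is 2.9% for the pooled test and 5.0% for CMH, so incomplete blocks soften the conservatism only slightly. With three strata, exact balance and shares of 20/40/40%, rates of 5/20/60% gain 11 to 13 points for odds ratios of 2 to 3. Fisher's exact test has lower power than chi-squared throughout.

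**Anchoring to the documented 29%.** Fix Arm 2 at 29% overall, with a SABR odds ratio of 2.5, three strata and shares of 20/40/40%. Let the cytotoxic v immunotherapy/targeted odds ratio set the gradient:

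| Gradient odds ratio | Power, pooled | Power, CMH | Gain (points) |
|---|---|---|---|
| 1.0 | 55.7% | 56.0% | 0.3 |
| 2.7 | 51.7% | 54.9% | 3.2 |
| 4.5 | 46.2% | 52.7% | 6.5 |
| 7.4 | 40.5% | 50.8% | 10.3 |

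Keeping the odds-ratio spread of 10/40/70% but shifting the rates so that Arm 2 is 29% (shares 25/35/40%) gives about 8 points at SABR odds ratios of 2.5 to 3.

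**The case against.** The planned test is valid. An unadjusted Fisher or chi-squared test is conventional for a secondary safety endpoint and easy to read, and the article claims no power for toxicity, so no stated property fails. All of that stands.

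A reader might infer that systemic therapy type is an established strong driver of toxicity here, and that the trial therefore loses about ten points of power. The article does not support this. It justifies the strata by prognosis and gives no toxicity rates by stratum. It restricts systemic agents around radiotherapy and discourages strong radiation enhancers soon after it, so a gradient is a reasonable inference, but its size is unknown. A ten-point loss needs steep assumptions: 10% v 70% is an odds ratio of (0.7/0.3)/(0.1/0.9) = 21 between strata.

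Grading toxicity for each treated organ may also point to radiation effects, which would flatten the gradient. Against that, toxicity is recorded at every visit in both arms, and the Analysis plan does not limit the comparison to irradiated organs. The wording leaves this open.

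Nor does protection against serious harm rest on this p-value. The DSMC reviews grade 3–5 cases and has discretionary thresholds of more than 40% grade 3 and more than 8% grade 5. That limits what is at stake.

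The worry that six strata with about 53 controls would cost power is answered by the flat-rate row: 74.8% v 74.7%.

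**Conclusion.** The point holds as a minor efficiency matter. The toxicity test ignores strata that the randomisation and the OS/PFS tests use. It never exceeds its nominal error, but it becomes conservative as toxicity diverges between strata, and so loses some power to show a SABR excess. The loss is about 0 points with flat or weak gradients, about 2 to 6 with moderate ones, and about 10 to 13 only with a strong gradient (14 in the steepest six-stratum scenario). These figures rest on assumed stratum shares and rates, a constant odds ratio and a two-sided 5% level. The loss would be smaller if only irradiated organs count. It would be wrong to conclude that the planned test is invalid or that a ten-point loss is expected.

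**What to change.** In the Analysis plan, replace the pooled comparison of grade 2+ toxicity with a Cochran-Mantel-Haenszel test stratified by histology group and systemic therapy type, using the exact version if cells are sparse. Report the stratified risk difference with its 95% CI. This changes one sentence and needs no extra patients or data. If stratum rates prove flat, it costs essentially no power.

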### Data safety monitoring committee

The DSMC membership will be independent of the study sponsor and free of competing interests. The DSMC will meet annually after study initiation to review toxicity outcomes. If any grade 3–5 toxicity is reported, the DSMC will review the case notes to determine if such toxicity is related to treatment. If the DSMC deems that toxicity rates are excessive (> 40% grade 3 toxicity, or > 8% grade 5 toxicity), then the DSMC can, at its discretion, recommend cessation of the trial, dose adjustment, or exclusion of certain treatment sites and/or delivery techniques that are deemed as high-risk for complications.

### Interim analysis

The DSMC will conduct one interim analysis once the 75th patient is accrued and followed for 6 months. For this interim analysis, the DSMC will be blinded to the identity of each treatment arm, but median OS data will be presented for each arm. The DSMC will recommend stopping the trial if there is an OS difference that is statistically significant with a threshold of *p* < 0.001 using the stratified log-rank test.

It is deemed worthwhile to stop for futility if both the OS and PFS analyses are likely to be negative. Therefore, at this interim analysis, if the hazard ratios for OS and PFS in Arm 2 vs Arm 1 are BOTH > 1.0 (i.e. a higher hazard rate for OS in the experimental arm, and a higher hazard rate for PFS in the experimental arm) using univariable Cox regression, then the trial will be stopped for futility.

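### The futility hazard ratios come from a treatment-only Cox model, while the analyses they are meant to foresee are stratified by histology and systemic therapy; adjusting them is a free, small improvement

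*Protocol article*

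**What the plan says.** The Interim analysis section sets two rules for one look, taken once the 75th patient has been accrued and followed for 6 months. For efficacy, the monitoring committee recommends stopping if the OS difference reaches p < 0.001 "using the stratified log-rank test". For futility, the condition is "if the hazard ratios for OS and PFS in Arm 2 vs Arm 1 are BOTH > 1.0", estimated and acted on as follows: "using univariable Cox regression, then the trial will be stopped for futility". The stated rationale is that stopping is worthwhile when the OS and PFS analyses are both likely to be negative.

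The Analysis plan section describes those two analyses: Kaplan-Meier estimates "with differences compared using the stratified log-rank test". The stratification factors are set out under Study design, below Fig. 1: histology in two groups and pre-specified systemic therapy in three. The protocol introduces them with "Patients will be stratified by two of the strongest prognostic factors". The Randomization section gives 1:2 allocation in permuted blocks, with the next assignment drawn for the patient's own stratum.

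**The concern.** The futility rule exists to foresee the failure of two stratified analyses, yet it reads the direction of effect from a model that ignores the strata. In a Cox model, leaving out strong prognostic covariates pulls the treatment hazard ratio toward 1, even when the arms are balanced, and makes the direction of effect less certain. The value 1 is also the futility cut-point.

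This rule also leaves the least discretion. Efficacy leads to a recommendation and toxicity limits are applied at the committee's discretion, but futility is worded as a stop. The decision depends only on which side of 1.0 two estimates fall, with about 44 deaths expected under the design effect. The protocol fixes the model itself, so this is not a detail left to an analysis plan.

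**Working it through.** **1. The plan's own figures.** Inputs from Sample size calculation and Randomization: median OS 10 v 17 months, alpha 0.05 (two-sided assumed, since sidedness is not stated), 80% power, 5% dropout, 1:2 allocation, 60 months of accrual plus 12 of follow-up.

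- Hazard ratio under exponential survival: 10/17 = 0.588, log −0.531.
- Schoenfeld events: (1.960 + 0.842)² / [(1/3)(2/3)(0.531)²] = 125.4, so 126. At the stated 122 events, power is 0.789.
- Probability of death by analysis: 0.897 (Arm 1) and 0.771 (Arm 2), weighted 1/3 and 2/3 = 0.813.
- Expected events: 159 × 0.95 × 0.813 = 122.8, against 122 stated.

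The design is reproduced, so 0.588 is a fair design effect for the interim.

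**2. The interim look.** About 44 deaths are expected among the first 75 patients at hazard ratio 0.588, and 52-53 at hazard ratio 1. Controls number 75 × 1/3 = 25, or 25/6 ≈ 4 per stratum.

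**3. Simulation of the rule (both hazard ratios > 1.0), univariable v covariate-adjusted Cox.** 2,500 looks per scenario. Assumptions not in the protocol: blocks of 6 within strata; histology split 40/60; systemic therapy split 40/40/20; accrual 2.65 per month (159/60); the same hazard ratio for progression and death; control median PFS about 5 months; prognostic hazard ratio 1, 2 or 3 per factor (for systemic therapy, the contrast between extreme groups).

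| Prognostic HR per factor | Decisions differ, true HR 1 | Median OS log-HR at design effect (univariable v adjusted) | Wrongful stops at design effect (univariable v adjusted) |
|---|---|---|---|
| 1 | 4.8% | – | – |
| 2 | 10.3% | −0.50 v −0.56 | 1.2% v 1.0% |
| 3 | 13.4% | −0.44 v −0.56 | 1.7% v 0.8% |

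The first row is the noise baseline. The part due to prognosis is 10.3 − 4.8 = 5.5 points at 2, and 13.4 − 4.8 = 8.6 points at 3. Monte Carlo standard error near 1% is √(0.01 × 0.99/2500) = 0.2 points.

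**4. Second, independent run, same layout, prognostic hazard ratios 2 to 3.** Decisions at true hazard ratio 1 differ in 9-13% of trials, against 5% when the factors are not prognostic. Wrongful stops at 0.588 go from 0.9-1.4% to 0.8%. Correct stops at a true hazard ratio of 1.3 rise from 69-72% to 71-73%. Over both runs, decisions under the design effect differ in about 0.4-1.4% of trials.

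**5. Full six-cell stratification instead of covariates.** 3,000 looks per scenario, blocks of 3 and 6. Decisions at true hazard ratio 1 differ from the univariable model in 9.6%, 12.9% and 14.7% of trials at prognostic hazard ratios 1, 2 and 3. The baseline is twice that of covariate adjustment (9.6% v 4.8%), because about four controls per cell carry little information. At prognostic hazard ratio 2, wrongful stops are 1.0% under either model.

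**The case against.** The strongest reply is that the design already protects against the obvious danger. A reader might infer that the stop can turn on chance prognostic imbalance in these two factors. The documents do not support that as the main mechanism, because allocation is blocked within the strata. With prognostic hazard ratios of 3 for both factors and the design effect, wrongful stops would be 3.3% (unstratified) v 1.6% (stratified) under simple randomisation, but are 1.6% v 1.3% under stratified blocks. Imbalance on other factors would not be cured by this fix either.

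Second, a reader might infer that attenuation causes false futility by itself. It does not: it shrinks the expected hazard ratio toward 1.0 without carrying it across, and the univariable medians of −0.50 and −0.44 stay well below zero. Both endpoints must also cross.

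Third, the disagreement at a true hazard ratio of 1 occurs where neither decision is clearly wrong, and part of it is noise. That stands, and the 9-13% must be read against its baseline of about 5%.

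Fourth, a covariate-adjusted Cox model is not the final stratified log-rank test either, and a simple directional check with about 44 deaths is defensible. This stands in part. A stratified Cox model would match the final test more closely, but it discards more information at this size. Covariate adjustment conditions on the same factors, and the Analysis plan already uses multivariable Cox regression for another purpose.

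What survives is an unexplained mismatch with a small cost in precision.

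**Conclusion.** The point holds as a minor, free improvement. The futility model is the only one of the between-arm OS and PFS comparisons fixed in the Interim analysis and Analysis plan sections that ignores the stratification factors, and it drives the mandatory stop. The cost is an attenuated, less precise hazard ratio near the cut-point. It is not confounding by stratum imbalance and not a materially inflated rate of wrongful stopping.

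Under the design effect, adjustment moves wrongful stops from about 0.9-1.7% to 0.8-1.0%. At moderate prognostic strength that gain is about one Monte Carlo standard error (1.2% v 1.0%); it is clearer only at a prognostic hazard ratio of 3. The gain in correct stops at a hazard ratio of 1.3 is one to two points. All of this rests on assumed prognostic strength, stratum shares, block size and PFS, none of which the protocol gives. The mismatch in the text depends on none of them.

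**What to change.** In the Interim analysis section, replace the univariable Cox regression with a Cox model containing treatment, histology group and systemic therapy group as covariates, for both OS and PFS. Keep the 1.0 thresholds and the requirement that both be exceeded. This adds three parameters (one for histology, two for systemic therapy). If the sponsor prefers the treatment-only model, one sentence giving the reason would settle the inconsistency.

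The cost is a few words in an amendment, best made before interim results by arm are seen. The factors are already recorded for randomisation, so no added data or patients are needed, and no covariate-adjusted scenario above showed a material rise in wrongful stopping.

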### Future pooled analysis with SABR-COMET-3

A separate but similar phase III trial, but for patients 1–3 metastases, called SABR-COMET-3, is being proposed and drafted at the same time as this current trial. Once both trials are complete, a separate pooled analysis, using individual patient data from both trials, will be conducted, with the primary endpoint of OS, and any of the secondary endpoints from either trial where data has been collected in both trials.

## Biomarker studies

The mandatory translational component of this trial has been designed to minimize the impact on patients while addressing important research questions around the oligometastatic state. Specifically, the increased requirements, beyond standard of care testing, consist of drawing 3 tubes of blood at 3 time periods (Fig. 2) for all patients: at randomization, 3-months post-randomization, and at progression.

**Fig. 2 Fig2:**
[figure not shown]
Peripheral Blood Collection Timeline. Study completion is defined as 5 years of follow-up. Sample 1A & 1B will include 2 vials of blood for ctDNA and peripheral blood mononuclear cell isolation

Patients in Arm 2 only also require a blood draw 1–3 days after their first fraction of SABR and then 1–4 weeks after completion of SABR, prior to systemic therapy. In patients who do not progress, the final sample will be drawn at study completion (5-years post randomization).

Blood sample collection must take place on Monday, Tuesday, Wednesday or Thursday such that biospecimens requiring immediate overnight shipping (CTCs) can be received and processed quickly, without samples sitting unprocessed over a weekend.

Specimens 1A and 1B are required only for patients in Arm 2 and consist of 2 tubes of blood for ctDNA (plasma) and peripheral blood mononuclear cells (PBMCs). The timing of these blood draws can be chosen to minimize visits for the patient, but must occur within 1–3 days after the 1st fraction of SABR and 1–4 weeks post-SABR (prior to systemic therapy), respectively. For example, since many patients will likely be receiving multiple single-fraction treatments over > 1 day or will be receiving 3- or 5-fraction SABR, the 1A blood draw can be completed upon a patient’s return for the second SABR treatment. This blood draw is preferred to occur on the day after the first fraction. Similarly, since many patients will be proceeding to systemic therapy within a few weeks of SABR, completing the 1B blood draw on the first day of systemic therapy, but prior to the delivery of the systemic therapy, would be reasonable.

In addition to blood samples, the study will collect tissue samples from previous biopsies or resections of the primary tumor and metastases, where available. No additional biopsies will be needed for the purposes of the biomarker component of this trial beyond those collected as part of routine clinical care. If formalin-fixed paraffin-embedded (FFPE) tissue blocks are not available to be sent at the discretion of the local pathologist (e.g. insufficient tissue, or a need to keep all tissue for future purposes), the FFPE tissue blocks are not required and centres can proceed by sending peripheral blood only.

### Laboratory support and shipping

Each participating institution will require an on-site laboratory for peripheral blood sample processing. This laboratory must also have freezer storage (− 80 °C and liquid nitrogen). The protocols for collection and processing of peripheral blood, including required equipment and reagents, are provided in the Laboratory Manual. All shipping costs will be covered via the provision of pre-paid shipping labels, and an additional small stipend will be provided to cover laboratory time. A ‘biomarker studies kit’ containing collection tubes and pre-paid shipping labels will be sent to each participating institution to be retained by the personnel responsible for biospecimen collection.

### Translational studies: Background & Rationale

At the present time, there are no biomarkers that define the oligometastatic state. The closest to a defining biological feature is tumor histology, of which breast, kidney, and prostate are associated with improved OS in patients with clinical oligometastatic disease [3]. Key clinical characteristics - colloquially termed ‘The Four Aces’ [20] - help to identify a patient sub-population with metastatic cancer that is most likely to benefit from ablation of all sites of disease.

Even within this group, however, outcome can be variable: while some patients exhibit long disease-free intervals and better-than-expected overall survival following ablation of metastases, others progress rapidly and extensively with poor survival outcomes [21]. Elucidating the biological mediators underlying a more indolent, sequential pattern of progression (i.e., oligometastasis) versus rapid, “poly-metastatic” progression will allow for more accurate selection of patients whose intrinsic natural history of disease make them more likely to benefit from ablation.

Specific biological characteristics of oligometastatic disease could provide important predictive biomarkers in this setting, but have thus far remained elusive. Studies up to this point have focused on micro-RNA profiling, but unfortunately these studies have not identified an miRNA expression signature that consistently defines patients with few metastases [22–24]. No other studies to our knowledge have sought to identify specific biomarkers of oligometastasis. While a wide array of pre-clinical analyses have identified genetic and epigenetic alterations associated with metastasis in general [25], it remains to be determined which of these features represent useful biomarkers in differentiating rapid and widely metastatic cancer from an oligometastatic natural history.

